## Abstract

**Background:**

Web-based nutritional education programmes appear to be comparable to those delivered face-to-face. However, no existing web-based nutrition education or similar programme has yet been evaluated with consideration of socio-economic status. The objective of a nutritional education programme of promoting vegetable intake designed a randomized controlled trial (RCT) is to evaluate the results of intervention and to determine how socio-economic status influences the programme effects.

**Methods/Design:**

Participants will be randomly sampled individuals (aged 30–59) stratified according national population statistics for sex, age, and household income. Participants were consented to survey participation (*n* = 1500), and will be randomly divided into intervention and control groups. The intervention period is 5 weeks with one step of diet-related education per week. The main outcome of the programme is dietary behaviour as eating vegetable (350 g per day, five small bowl). To encourage behavioural changes, the programme contents are prepared using behavioural theories and techniques tailored to the assumed group stages of behavioural change. In the first step, we employ the health belief model to encourage a shift from the pre-contemplative to the contemplative phase; in the second and third steps, social cognitive theory is used to encourage transition to the preparatory phase; in the fourth step, social cognitive theory and strengthening social support are used to promote progression to the execution phase; finally, in the fifth step, strengthening social capital and social support are used to promote the shift to the maintenance phase. The baseline, post intervention and follow-up survey was assessed using a self-administered questionnaire. For process evaluation, we use five items relating to programme participation and satisfaction. A follow-up survey of participants will be carried out 3 months after intervention completion.

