## Methods

### Study design

This study describes a two-armed, matched-design, web-based RCT. The nutrition education programme that we have developed as part of a health promotion project (Fig. 1). The intervention period is 5 weeks. The RCT is designed in line with the CONSORT statement for randomised trials of non-pharmacologic treatment [28]. Participants were assessed at three points in time: at baseline (T1), at post intervention (5 weeks later; T2), and at a follow-up at 3 months (T3). The participants were randomly assigned to one of two conditions: the intervention group and the waiting list group (i.e., the control group).

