### Study sample

#### Recruitment source and procedure

A web-based intervention survey was conducted by a Japanese online research service company that contains data, including sociodemographic attributes, for approximately 160,300 adults aged 30–59 years. Participants were randomly selected based on Japanese population statistics for the present study. We targeted adults because of the necessity of health promotion, healthy eating, and reduction in health disparities for this age group [23]. The following inclusion criteria are considered: (1) men and women aged 30–59 years old; (2) able to understand Japanese; (3) can access the Internet at home, work, or a public place; (4) agree to access the study website during the 5-week intervention period; (5) will participate in all three assessment points during the 4-month study period. The exclusion criterion is having an household income of ten million yen or more (meaning that 88.4% of the total population is having an household income of ten million yen less) [29]. The study procedure from enrolment to follow up is depicted in Fig. 1.

The research company that we used in the present study periodically analyses and updates its registrant database. A notable characteristic of this company is that, to prevent bias among survey respondents, the firm requests the participation of the minimum number of respondents after taking response rate into consideration. Moreover, once every 6 months, the firm updates its monitoring information and conducts checks to safeguard against double registration or non-existent IP addresses. Registrants had been enrolled with the survey company by an open recruitment process.

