### Setting

Regarding the setting, at baseline (T1), individuals consenting to participate in the study were randomly assigned it to two groups in the order that received an answer to the intervention or control groups by the online research service company. The researchers were not involved in this allocation in any way. All participants received a notification e-mail informing them of their allocated groups. The groups were listed as P Group (intervention group) and Q Group (control group) to prevent participants from knowing which group they were assigned to. This study is signal a type of single blinding. Because it is not the intervention of face to face, there is no contact during the intervention period.

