### Sample size

The sample size was calculated using G*Power [50]. We set an effect size of 0.5, an α of 0.05, and a power of 0.95. With the expectation that two-thirds of participants would drop out, the size of the intervention group was set at 900 subjects, while that of the control group was set at 600 subjects with the expectation that a half of participants would drop out. Furthermore, we aimed to divide the intervention and control groups further according to income (low and high).

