### Statistical analyses

All statistical analyses will be performed with IBM SPSS Statistics 21.0. For continuous variables, independent t-tests will be used to determine inter-group differences and Man–Whitney U-tests for intra-group comparison, while the χ^2^ or an equivalent test is to be used to determine the associations between categorical variables. Because this is a prospective RCT involving repeated measures, repeated measures analyses of variance will be applied to determine significant differences within the study groups. We also considered the possible effect of time on groups. The evaluation of the intervention is based on an intention-to-treat analysis. A *p*-value of 0.05 has been set as the level of significance.

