The RCT in this study is original in the following two regards. (1) It can verify the intervention effect for an adequate sample size, and (2) it can verify differences in the effect of a nutrition education programme by income strata. With this study, it will also be possible to verify the possible catch-up effect in relation to undesirable vegetable intake behaviour associated with low household income. Some reports have suggested that traditional classroom-based nutrition interventions might widen this disparity [6]. In contrast, with our study, it may be possible to show that a web-based nutrition education programme would inhibit the widening of this disparity.

Conversely, this study also has its limitations. It is possible that the results of the study will reflect the characteristics of individuals registered with the research company (e.g., tending to be young, high-earning, and highly educated [51–53]). To minimize this potential limitation, we have made sure to match participants with demographic distributions in terms of sex, age, and household income. In addition, we requested research cooperation from individuals whose household income data – which was our objective – had been recorded in advance. This helps to restrict attribute bias as well as negative response rates for delicate questions pertaining to household income and other matters. Second, during participant recruitment, we excluded individuals reporting household incomes of ten million JPY or more. This means that the results do not target the entire population. Accordingly, care must be taken when drawing general conclusions. However, a limit of less than ten million JPY still applies to 88.4% of the Japanese population. Finally, participants did not have contact with one another (either in person or through indirect communication) for the period of the intervention. For this reason, it is possible that rates of adherence to nutrition education programmes will be lower than they would with enforced participation.

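### The stated between-arm t-test has no income, sex or age term, although the sample is drawn on all three and income is on file before randomisation; adding them is a modest, free gain

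*Protocol article*

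**What the plan says.** The abstract (Methods/Design) sets out the sampling: "Participants will be randomly sampled individuals (aged 30–59) stratified according national population statistics for sex, age, and household income". Recruitment source and procedure says the research company's database "contains data, including sociodemographic attributes, for approximately 160,300 adults aged 30–59 years". Strengths and limitations adds that income was known beforehand: "we requested research cooperation from individuals whose household income data – which was our objective – had been recorded in advance".

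Study design labels the trial a "two-armed, matched-design, web-based RCT". The only matching described anywhere is of the sample to national distributions. Setting describes the allocation of those who consented as follows: "randomly assigned it to two groups in the order that received an answer to the intervention or control groups by the online research service company". No stratification factor is named there.

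Sample size states an aim to "divide the intervention and control groups further according to income", and the Background makes the effect by socio-economic status a secondary objective. Statistical analyses gives the between-arm method for continuous variables: "independent t-tests will be used to determine inter-group differences". It adds χ² tests, repeated measures analysis of variance for differences within the groups, and an intention-to-treat evaluation. None of these is given an income, sex or age term.

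**The concern.** By the protocol's own account, income predicts the outcomes. The Background reports daily vegetable intake 70 g lower in lower-income than in higher-income groups, the same size as the hypothesised programme effect. Primary outcomes says self-rated health is associated with socio-economic status. A prognostic factor known before randomisation belongs in the between-arm model. Leaving it out gives up precision, and it gives up protection if those analysed differ in income between the arms.

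The second matter is live because Sample size expects unequal drop-out. Strengths and limitations suggests that matching the sample to national distributions deals with most confounding at allocation. It does not: a representative sample can still be split into arms that differ in income.

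**Working it through.** **Inputs from the protocol.** 900 intervention and 600 control participants; expected drop-out of two-thirds and one-half; effect size 0.5 (Sample size). Income gap of 70 g per day (Background).

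**Assumptions not in the protocol.** Half the sample is low-income (20% as a variant). The 70 g gap applies between the two halves of this sample. The standard deviation (SD) of daily intake is 100 to 200 g. Retention by income is as in step 4.

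1. **The plan's completers.** 900 × 1/3 = 300 and 600 × 1/2 = 300.

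2. **Chance imbalance in low-income share.** SE = √[p(1 − p)(1/n₁ + 1/n₂)].
   - All randomised, p = 0.5: √[0.25 × (1/900 + 1/600)] = 0.0264, so the 95% range is ±1.96 × 0.0264 = ±5.2 points. Multiplied by 70 g this is 3.6 g.
   - All randomised, p = 0.2: SE 0.0211, range ±4.1 points.
   - 300 v 300 completers, p = 0.5, drop-out unrelated to income: √[0.25 × 2/300] = 0.0408, range ±8.0 points, or 5.6 g.

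3. **Variance explained by income.** A 70 g gap between equal halves puts each half 35 g from the mean, so R² = (35/SD)².

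| Intake SD (assumed) | R² | SE after adjustment, √(1 − R²) | Power at standardised effect 0.2, 300 per arm |
|---|---|---|---|
| 100 g | 0.122 | 0.937 of unadjusted | 0.69 → 0.74 |
| 150 g | 0.054 | 0.972 of unadjusted | 0.69 → 0.71 |
| 200 g | 0.031 | 0.985 of unadjusted | 0.69 → 0.70 |

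   The effect of 0.2 is illustrative. At the planned 0.5, power with 300 per arm already exceeds 0.99, so the precision gain matters only if the true effect is smaller.

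   Steps 2 and 3 describe the same quantity. At SD 150 g the 95% margin for 300 v 300 is 1.96 × 150 × √(2/300) = 24 g, and (5.6/24)² = 0.054, which is the R² for that SD. Chance imbalance is therefore already inside the t-test's standard error and must not be counted again as bias.

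4. **Drop-out that depends on income (illustration only).** Suppose 450 low-income and 450 high-income participants in the intervention arm are retained at 25% and 41.67%: 112.5 + 187.5 = 300 completers, 37.5% of them low-income. If controls are retained at 50% in both groups, their share stays at 50%. An unadjusted comparison of completers' intake levels is then shifted by (0.50 − 0.375) × 70 = 8.75 g in favour of the programme. With retention of 20% and 46.67% the share is 30% and the shift is 0.20 × 70 = 14 g. If retention does not depend on income, the shift is zero. An income term compares like with like and removes the shift, provided drop-out within each income group is unrelated to the outcome.

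**The case against.** A reader might infer that neither allocation nor analysis uses the sampling strata, and that income balance is left to chance. The documents do not support that. An income comparison is planned in the Background, in Sample size and in Strengths and limitations. The account of allocation names no strata but does not exclude them, and an article may leave such detail to the full protocol. All that can be said is that stratified allocation is not described.

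Sampling strata need not be randomisation strata. Simple randomisation of 1500 people is valid, and so are comparisons within an income group. Under simple randomisation with half the sample low-income, the number of low-income people in the intervention arm would lie between 431 and 469 in 95% of allocations. That raises the variance of the low-income effect by at most about 2.4%.

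The gram figures also have limits:
- The 25%/42% retention is assumed; the protocol gives no drop-out by income.
- The 70 g gap is between income groups in the population, whereas the trial excludes household incomes of ten million yen or more.
- Grams of vegetables are a secondary outcome in the Methods, and nothing here quantifies the effect on the primary outcomes.
- A constant income gap cancels from change since baseline. This helps only for outcomes measured at T1, and the Assessment section leaves unclear whether the eating behaviours are.

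All of this stands, and it limits the size of the point. What remains is that the article does state a between-arm method, and that a better one is available from data already held.

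**Conclusion.** The point holds as a low-priority improvement. The stated between-arm comparison is unadjusted, although income is known in advance and treated by the protocol as prognostic, and although unequal drop-out is expected. Matching the sample to the population does not itself balance the arms.

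The trial is not invalidated. Chance imbalance at randomisation is about ±5 points of low-income share if half the sample is low-income. The precision gain is roughly 3% to 12% of outcome variance for an assumed intake SD of 200 to 100 g and a 70 g gap between halves. Any removal of bias depends on how far drop-out is related to income, which the documents do not say; the shift of about 9 g is an illustration, not an estimate. It would be wrong to conclude that missing stratification at allocation biases the trial. Nor would stratified allocation prevent income-related drop-out.

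**What to change.** In Statistical analyses, replace the independent t-test as the between-arm comparison with a linear model, or the repeated-measures model, that includes baseline income stratum, sex and age band as fixed terms. State this before the outcome data are examined.

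Stratified allocation by income is optional and relevant only if allocation is still open; the Setting section describes assignment in the past tense.

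The cost is a sentence or two in the analysis section. No extra participants or data are needed, because the research company's database and the baseline questionnaire already supply the terms.

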**Discussion:**

The fact that this study is an RCT with an established control group is a strong advantage. Information and communications technology is not limited by time or place. If we could show this web-based nutrition education programmes has a positive effect, it may be an appropriate tool for reaching individuals in lower socio-economic state.

**Trial registration:**

Current Controlled Trials UMIN-ICDR UMIN 000019376 (Registered October 16, 2015).

## Background

Appropriate vegetable intake appears to be effective for cancer prevention [1, 2] and is associated with reduced risks of cardiovascular disease [3, 4], obesity [5], and other lifestyle-related diseases. Health policy initiatives are promoting vegetable intake across all segments of the population worldwide. However, in practice, it has been widely reported that vegetable intake remains low among social disadvantaged groups in terms of household income and other indicators of socio-economic status [6, 7].

As part of efforts to promote vegetable intake among adults, several nutrition education programmes that have incorporated aspects of behavioural science theory have proven effective [8–10]. Web-based intervention programmes are of particular note, and several have been developed and verified outside of Japan [10–20]. Lauren et al. [17] compared the effects of face-to-face nutrition education with a web-based education, and found that changes in vegetable intake prompted by the web-based programmes were comparable with those achieved through the face-to-face programmes. Additionally, Bensley et al. [16] reported that provision of information through bulletins board increased vegetable intake by 0.2 serving while a web-based intervention increased intake by 0.6 serving.

Despite these promising findings, only the reports by Buller and Ball [13, 19] considered socio-economic status in relation to web-based nutrition education programmes, indicating an extreme paucity of research in this area. Buller et al. demonstrated that it is possible to implement web-based nutrition education programmes even in agricultural communities lacking an adequate web infrastructure. Of course, a remaining challenge is that their findings are limited to agricultural communities. There are no studies comparing the effects of different socioeconomic status.

In Japan, the recommended daily amount of vegetables is 350 g, from the perspective of preventing lifestyle-related diseases [21]. Nevertheless, approximately two-thirds of adults do not meet this recommendation [22] – in particular, the average daily vegetable intake for adults is around 70 g below the recommended amount. The average daily intake among lower-income social groups is a further 70 g lower than that among higher-income groups. Our nationwide survey of adults on the actual situation regarding the relationship between socio-economic status and dietary habits showed that, lower-income groups are less likely to have a habit of eating five servings of vegetables daily than are higher-income groups [23]. However, even among higher-income groups, the proportion of individuals who customarily consume five servings of vegetables daily is extremely small, at approximately 10% of the population [24]. Thus, support for the increased intake of appropriate vegetables should be implemented using a population-based approach that targets not only lower-income groups, but also the entire adult population. We hypothesize that achieving an approximately 70 g (1 serving) increase in vegetable intake might help lower-income groups to catch up while simultaneously contributing to the partial resolution of the deficient vegetable intake amongst Japan’s adult population.

In Japan, Ministry of Internal Affairs and Communications report on Internet usage by Japanese citizens [25] shows that, today, the proportion of Internet users among all Japanese aged 30–59 is 90% or more. Furthermore, the proportion of lower-income individuals (i.e., who are earning less than two million JPY per annum; approx. 15,800 GBP) is 61%, and rising annually. A relatively high proportion of respondents to this report indicated that they use the Internet to search for information about health and medicine, ranging from 73% among 30-year-olds to 80% among 59-year-olds. The proportion of respondents who reported using the Internet at least once a week was as high as 91%. Thus, as a form of information and communications technology (ICT), the Internet is a powerful health education tool for which future expansion can be anticipated in fields of health promotion, especially nutrition [26]. Web-based nutrition education programmes by their nature rely on ICT and the Internet in particular [27]. However, in the context of web-based support for increased vegetable intake, there are almost no reports, even at the worldwide level, verifying the effects of these programmes according to income level.

In this paper, we describe the methods and protocol of a randomized controlled trial (RCT) that seeks to verify the effectiveness of a web-based nutrition education programme of promoting vegetable intake among adults and that is based on behavioural science theory. The main objective of the RCT is to develop and verify the effects of a 5-week programme of promoting vegetable intake. A secondary objective is to determine how the effects of this web-based nutrition education programme differ according to socio-economic status.

## Methods

### Study design

This study describes a two-armed, matched-design, web-based RCT. The nutrition education programme that we have developed as part of a health promotion project (Fig. 1). The intervention period is 5 weeks. The RCT is designed in line with the CONSORT statement for randomised trials of non-pharmacologic treatment [28]. Participants were assessed at three points in time: at baseline (T1), at post intervention (5 weeks later; T2), and at a follow-up at 3 months (T3). The participants were randomly assigned to one of two conditions: the intervention group and the waiting list group (i.e., the control group).

### Ethics approval

The RCT was conducted according to guidelines laid out in the Declaration of Helsinki for procedures involving human subjects, and has been approved by the Ethics Review Committee on Research with Human Subjects of Waseda University, Japan (2015-167). The respondent's privacy and personal information are fully protected due to agreement between the registration monitor and the social research company used to recruit participants. All e-mails were sent to participants by the research service company, and we have received a database containing only non-specific, anonymized data.

**Fig. 1 Fig1:**
[figure not shown]
Flow chart showing participant recruitment, randomization, and evaluation of the Diet and Exercise Practices Project study

### Study sample

#### Recruitment source and procedure

A web-based intervention survey was conducted by a Japanese online research service company that contains data, including sociodemographic attributes, for approximately 160,300 adults aged 30–59 years. Participants were randomly selected based on Japanese population statistics for the present study. We targeted adults because of the necessity of health promotion, healthy eating, and reduction in health disparities for this age group [23]. The following inclusion criteria are considered: (1) men and women aged 30–59 years old; (2) able to understand Japanese; (3) can access the Internet at home, work, or a public place; (4) agree to access the study website during the 5-week intervention period; (5) will participate in all three assessment points during the 4-month study period. The exclusion criterion is having an household income of ten million yen or more (meaning that 88.4% of the total population is having an household income of ten million yen less) [29]. The study procedure from enrolment to follow up is depicted in Fig. 1.

The research company that we used in the present study periodically analyses and updates its registrant database. A notable characteristic of this company is that, to prevent bias among survey respondents, the firm requests the participation of the minimum number of respondents after taking response rate into consideration. Moreover, once every 6 months, the firm updates its monitoring information and conducts checks to safeguard against double registration or non-existent IP addresses. Registrants had been enrolled with the survey company by an open recruitment process.

Study participants were recruited using the following procedure. Of the approximately 160,300 registered monitors (as of September 2015), participants randomly to match the sex, age [30], and household income [29] distributions of Japan. Only study participants received an e-mail containing the website URL and password. Participate in the study were randomly assigned it to two groups in the order that received an answer to the intervention or control groups by the online research service company. The web-based nutrition educational programme is available in HTML format. Respondents who completed the questionnaire and clicked the ‘send’ button at the end of the online informed consent form were considered to have consented to survey participation (*n* = 1500). The research service company offered reward points valued at 40 JPY (in October 2015, one USD was equivalent to approximately 121 JPY) at T1. Of these, individuals who were allocated to the intervention group were offered reward points valued at 300 JPY after completion of the intervention (T2). Respondents from the control group were offered reward points valued at 40 JPY at T2. The participants were again offered reward points valued at 40 JPY for completing the assessment at 3 months after the completion intervention (T3; i.e. 4 months after the completion of the baseline survey [T1]).

